### Secondary outcomes

a. To compare differences between COS and TAU on maternal sensitivity (MBQS, DIP) as continuous secondary outcome variables, a 2x2 analysis of covariance (ANCOVA), with repeated measurement (t0-t1) on one first factor, will be used. In these analyses, treatment modality will be treated as the second factor, maternal sensitivity as the dependent variable, and maternal psychopathology (BDI, SCL-90-R) and maternal parenting stress (PSI) as co-variables.

b. To compare differences between COS and TAU on maternal mentalization (RF, PRFQ-1) as continuous secondary outcome variables, a 2×2 analysis of covariance (ANCOVA), with repeated measurement (t0-t1) on one first factor, will be used. In these analyses, treatment modality is to be treated as the second factor, maternal mentalization as dependent variable, and again, maternal psychopathology (BDI, SCL-90-R) and maternal parenting stress (PSI) as co-variables.

c. Furthermore, in a multiple linear regression, the differences in maternal sensitivity and mentalization will be used to predict psychopathology and maternal stress (with treatment modality, differences in psychopathology, and differences in maternal distress as independent variables).

d. Before analyzing the proportions of mothers whose attachment representations change during the treatment and follow-up period in both treatment arms, we will separate those mothers with a positive shift in attachment representations [i.e., insecure (-dismissing, preoccupied, unresolved) to secure) from the mothers without such a shift or with a negative one ((i.e., secure to any of the others)]. For binary responses, a binary logistic regression will be used to compare proportions of mothers whose attachment representations (positive shift vs. no/negative shift) have been altered as a criterion variable, and treatment group (COS vs. TAU), differences of maternal psychopathology (BDI, SCL-90) as well as parenting stress (PSI) prior and after treatment as predictor variables.

e. To examine associations between changes of psychopathology (BDI, SCL-90) and changes in parenting stress (PSI) between pre- and post-assessment, a Pearson correlation analysis with the difference scores will be conducted.

f. Child behavior and emotional problems (CBCL11/2) at follow-up will be analyzed with respect to mean scores in either arm of the trial, using multiple linear regression analyses. Again, maternal psychopathology (BDI, SCL-90) and maternal parenting stress (PSI) will be treated as predictor variables, in addition to treatment modality.

g. Further multiple regression analyses will be conducted, with mean changes in maternal sensitivity (MBQS, DIP), mentalization (RF, PRFQ-1), and maternal attachment representations (positive shift, no/negative shift) before and after treatment, as predictor variables.

h. Binary logistic regression models will be used to compare proportions of child attachment security (vs. insecurity) at follow-up as criterion variables, using treatment modality, maternal sensitivity, maternal self-reflection (RF), maternal psychopathology (BDI, SCL-90), and maternal parenting stress (PSI) as predictor variables.

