#### Circle of Security (COS) intervention

The Circle of Security (COS) intervention
[64,67] was designed to alter developmental pathways for at-risk parents and their children. In the current study, COS was only used with mothers, except for the single additional session with fathers/family members. It was conceptualized as a psychodynamically oriented, psychotherapeutic and community-based parenting program and is considered to be evidence-based in the USA. The COS is a treatment based on groups of six individuals. The group intervention focuses on the caregiver and his/her relational capacities in providing child–parent attachment security. The COS manual (unpublished) draws upon the work practiced in Early Head Start and Head Start programs in the USA and was developed by the originators
[68] at the Marycliff Institute in Spokane, WA. The COS therapists of the current trial underwent an intensive 10-day training in COS assessment and treatment organization at the Marycliff Institute in preparation for this study.

Prior to the beginning of the group therapy, a thorough diagnostic assessment of the interactions between mother and infant in various situations was performed, during which attachment and explorative behaviors were activated. Additionally, an interview with regard to caring for the child (the “Circle of Security” Interview;
[69]), as well as an attachment interview (Adult Attachment Interview, AAI;
[70]) were conducted with the mother. With the “Circle of Security” model as a foundation for intervention, an assessment of the relationship between mother and child was prepared with the help of video recordings and both interviews. From this assessment, the maternal core difficulty (termed the “linchpin struggle”) and the preferred (unconscious) defense strategy against potential threatening or uncomfortable emotions (procedural) or cognitions (termed “shark music”) connected with the attachment and autonomy needs of the child, were deduced. An individual treatment plan was formulated for each mother-infant-dyad,. This treatment plan contained a sampling of video sequences, which were used throughout the therapeutic process in order to acquaint the mother with her “linchpin struggle” whilst taking the mother’s “core sensitivity” and “shark music” into account. The “core sensitivity” describes an integral aspect of the personality

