[77] is utilized to measure maternal mentalizing, which is defined as the capacity of the mother to reflect upon her own self and close others in terms of intentional mental states. The RF allows for overall ratings of reflective functioning on a nine-point scale ranging from 1 (lacking RF) to 9 (exceptional RF), with two additional RF scores indexing the absence of mentalizing, that is, -1 (negative RF), 0 (lacking RF). RF-ratings will be performed on the AAI obtained at baseline and follow-up by two independent raters blind to treatment allocation.

**PRFQ-1 –** The Parental Reflective Functioning Questionnaire-1
[78] is used as an alternative instrument for assessing RF via self-report. The PRFQ-1 assesses the levels of parental mentalization up to the child’s age of 3 years. It consists of 39 items comprising three subscales prototypically describing high, low, and neither high nor low mentalizing in mothers and fathers. Scoring procedures precepts yield a total score on all three subscales. PRFQ-1 is administered at baseline and follow-up.

**SCID-I** – The German version of the Structured Clinical Interview
[79] for DSM-IV
[80] axis I disorders is used to verify clinical DSM-IV-Axis-I diagnoses. SCID-I interviews were conducted by trained researches at baseline.

**SCID-II** – The German version of the Structured Clinical Interview (SCID-II) for personality disorders is used to identify mothers with probable DSM-IV-Axis II personality disorders. SCID-II interviews were conducted by trained researchers at baseline.

**BDI** – The Beck Depression Inventory
[81,82] is administered to screen for depressive symptoms in the mothers at baseline and follow-up. It consists of 21 items, scaled from zero to three, which are summed to a global score, indicating clinical significance of self-reported depressive symptoms.

**SCL-90-R** – The revised Symptom Checklist by Derogatis
[83] (German version:
[84]) is used to assess maternal psychopathological symptoms. The Global Severity Index, as a sum score of the SCL-90-R, is applied to determine maternal psychopathology at baseline and follow-up.

**PSI** – The Parenting Stress Index
[85] (German:

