[86]) is a self-report measure consisting of 120 items for parents with children aged from 0–12 years, capturing child-related and parent-related stress domains. A total stress score is derived, indicating the severity of the subjective burden of parenting. A domain of life events allows for the recording of positive and negative life events. The PSI is measured at baseline and follow-up.

**DERS –** The Difficulties in Emotion Regulation Scale
[87] is a 36-item self-report on clinically relevant emotion regulation difficulties, especially with regard to negative emotions. Items are scored on a 5-point Likert scale ranging from 1 (almost never) to 5 (almost always). The authors have confirmed a six-factor structure of emotion regulation, upon which the DERS is based; and adequate internal consistency (Cronbach’s α > .80) of these subscales has been established
[87]. For the purpose of this trial, the DERS was translated into German. First, the scale was translated from English to German independently by two translators who then discussed their translations and combined them to form a draft of the questionnaire used in the present study. This draft was back-translated into English by a professional translator. The back-translated version was found to be consistent with the original DERS version. The DERS is applied at baseline and follow-up.

**CBCL** – The Child Behavior Checklist1½**-**5
[88] (German version) is a questionnaire for parents of children aged 1.5-5 years, which is used to assess child behavioral and emotional problems. The items are related to seven problem scales, loading on externalizing, internalizing, and a total score. In the current trial, the CBCL will be administered at follow-up.

**FBB-E** – Fragebogen zur Beurteilung der Behandlung – Eltern
[89] (“A Questionnaire to Evaluate Treatment Satisfaction – Parent Version”) is a well-known German language questionnaire for evaluation and quality assurance of the therapeutic treatment of children, adolescents and their families. The FBB-E assesses how positively or negatively parents evaluate the course and outcome, as well as their personal satisfaction regarding the psychotherapeutic treatment of their children, independent of treatment modality. The FBB-E will be applied at follow-up.

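### No listed analysis gives an interpretable COS–TAU difference in maternal depression, symptoms, parenting stress or emotion regulation, and item c has the same constructs on both sides of the model

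*Protocol article*

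**What the plan says.** Under Assessment and outcomes measures, Secondary outcomes, four maternal self-report scales are scheduled twice, and Table 1 agrees:

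- The BDI "is administered to screen for depressive symptoms in the mothers at baseline and follow-up".
- The SCL-90-R Global Severity Index "is applied to determine maternal psychopathology at baseline and follow-up".
- "The PSI is measured at baseline and follow-up".
- "The DERS is applied at baseline and follow-up".

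Under Statistical methods, Secondary outcomes, items a to h assign these scales their roles. Items a and b compare the arms on sensitivity and mentalization, with "maternal psychopathology (BDI, SCL-90-R) and maternal parenting stress (PSI) as co-variables". Items d, f and h place the same three scales among the predictors of, respectively, a positive shift in maternal attachment representation, CBCL scores and child attachment security. Item e looks at changes in BDI, SCL-90 and PSI: "a Pearson correlation analysis with the difference scores will be conducted". Item c states that "the differences in maternal sensitivity and mentalization will be used to predict psychopathology and maternal stress"; its bracket then names treatment modality together with change in psychopathology and change in distress as independent variables. Item g lists predictors but names neither a dependent variable nor treatment arm. DERS is in none of the eight items.

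**The concern.** A scale that is listed under secondary outcomes and measured before and after treatment in both randomised arms would normally get an estimate of the arm difference. Here the list uses three of the scales to adjust or explain other outcomes and leaves the fourth out. The one model with maternal symptoms and stress as the predicted variables is worded so that its treatment coefficient does not answer the question.

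The participants are mothers with mental disorder, and the Abstract says that maternal and child outcome data will inform hypotheses about which intervention may suit a psychiatric outpatient setting. If the list were followed as written, a difference between arms in the mothers' own condition, in either direction, would enter only as an adjustment or a correlation. The report could describe child attachment by arm without any estimate for the mothers' symptoms or stress.

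**Working it through.** **1. Does any item give an arm difference on these scales?**

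- a, b: the outcome is sensitivity or mentalization; BDI, SCL-90-R and PSI are covariates. No.
- c: the outcome is psychopathology and stress, and arm is included, but so are changes in the same constructs. See step 2.
- d, f, h: the outcomes are attachment shift, CBCL and child attachment; the scales are predictors. No.
- e: correlation among change scores, no arm term. Even if run within each arm, a correlation says nothing about a difference in level. No.
- g: no stated outcome, no arm. No.
- DERS: not named in any item.

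**2. What does the treatment term in item c estimate?**

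The documents give no variances or correlations, so these are assumptions: COS raises BDI and PSI by 0.5 SD; the within-arm SD is 1 at both times; baseline and follow-up correlate at r on each scale; BDI and PSI correlate at 0.6. Changes in sensitivity and mentalization, which item c also includes, are left out for simplicity. The arm difference in change is then 0.5 for both scales.

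- Outcome is follow-up BDI; predictors are arm, BDI change and PSI change. Within arm, Cov(follow-up, change) = 1 − r and Var(change) = 2(1 − r), so the slope on BDI change is 1/2 for any r, and the slope on PSI change is 0. Arm coefficient = 0.5 − 0.5 × 0.5 = 0.25.
- Outcome is BDI change; same predictors. The outcome is its own predictor, so the arm coefficient is 0.
- Outcome is BDI change; predictors are arm and PSI change only. The slope on PSI change is 0.6. Arm coefficient = 0.5 − 0.6 × 0.5 = 0.20.
- Follow-up BDI on arm and baseline BDI (ANCOVA). Arm coefficient = 0.50.

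A simulation of 400,000 dyads at r = 0.3, 0.5 and 0.7 agreed: 0.244 to 0.258, 0, 0.200 to 0.203, and 0.496 to 0.503 respectively.

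**3. How precise would a direct comparison be?**

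The article states no precision for any maternal scale. Limitations gives 36 dyads per arm. In SD units, the half-width of the 95% CI is 1.96 × √(2/n) × √(1 − r²). With n = 36, 1.96 × √(2/36) = 0.462.

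- r = 0.3: 0.462 × 0.954 = 0.44
- r = 0.5: 0.462 × 0.866 = 0.40
- r = 0.7: 0.462 × 0.714 = 0.33

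With the 40 per arm given in the Abstract, r = 0.5 gives 0.38. With an assumed 29 per arm after drop-out, r = 0.5 gives 0.45. At 36 per arm and r = 0.5, the difference detectable with 80% power is (1.96 + 0.84) × 0.866 × √(2/36) = 0.57 SD, and power for a true 0.5 SD difference is 69%.

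COS is delivered in six groups of six. Any positive correlation within groups widens these intervals; the article gives no intraclass correlation, so no figure is attached.

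**The case against.** The case on the other side has real content. The secondary-outcomes heading works partly as a catalogue of measures, since it includes SCID-I and SCID-II, which are taken only at baseline. The secondary hypotheses concern sensitivity, mentalizing and state of mind, and the Abstract gives psychopathology a moderator or mediator role, so using BDI, SCL-90-R and PSI as covariates fits those aims. Item c may simply be inverted wording. This is a condensed article, and the absence of DERS from the list could on its own be left to a fuller plan.

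That limits the point but does not remove it. The article does not merely stay silent: it enumerates the analyses, gives three of the scales explicit roles, and writes one model for psychopathology and stress that contradicts itself. Whichever reading of item c was meant, the text as printed needs correcting.

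Two stronger readings are tempting, and the documents support neither. A reader might infer that the trial cannot show whether COS makes mothers worse. That is wrong: randomised measurements before and after treatment exist in both arms, and a direct comparison can be made from them. A reader might also infer that worsening is a foreseeable harm of COS, because the preparatory assessment identifies "the preferred (unconscious) defense strategy against potential threatening or uncomfortable emotions". That sentence describes a diagnostic formulation. The same section describes individual treatment plans, two therapists per group and weekly supervision, and nowhere says that symptoms may worsen. The case for estimating the arm difference does not need that premise.

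A single follow-up at child age 16–18 months would also miss any transient change during the weekly sessions, so the added estimates should not be presented as a full account of harms.

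**Conclusion.** The point holds as a gap in the listed analyses. None of items a to h gives an interpretable COS–TAU difference on BDI, SCL-90-R, PSI or DERS, and item c is mis-specified rather than absent. Under the assumptions shown, its treatment term would report half of a true 0.5 SD difference or none of it. Those sizes depend on the assumptions; the overlap between outcome and predictors does not.

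The primary test and the hypothesised secondary comparisons are untouched. What is missing is a statement of the mothers' own condition by arm, which could be estimated to within about 0.33 to 0.44 SD at best. Observed differences near zero could then exclude only moderate-to-large worsening.

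**What to change.** Make two changes to the secondary analyses.

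1. Restate item c so that no construct appears as both outcome and predictor, and say whether the outcome is the follow-up score or the change. If changes in sensitivity and mentalization stay in as explanatory variables, describe the model as exploratory and do not read its arm term as the treatment effect.
2. Add an item: for BDI total, SCL-90-R Global Severity Index, PSI total and DERS, estimate the COS–TAU difference at follow-up by randomised arm, using ANCOVA on the baseline value of the same scale plus the infant-age stratum used in randomisation, with a 95% CI. The article describes the DERS by its six factors, so fix in advance which DERS score is used. Present the four results as secondary estimates without a confirmatory claim, and state that a null result at this sample size does not show absence of worsening.

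The cost is four models and one table on data already collected, with no new visits or measures.

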### Aims and hypothesis

The primary aim of this study is to evaluate the efficacy of COS versus TAU in mothers with mental disorder and their infants in promoting attachment security in the child under standard clinical outpatient conditions. More specifically, the goal of the study is to determine whether COS intervention results in more securely attached infant–mother dyads than the control condition (TAU). The primary hypothesis is that the COS intervention will bring about a higher rate of securely attached children after treatment and at follow-up (when the children are aged 16–18 months) than TAU. Secondary hypotheses being tested by the study are that i) COS intervention will lead to an increase in sensitive behavior in mothers, ii) COS intervention will result in an increase in mothers’ ability to mentalize, and iii) COS intervention will improve mothers’ state of mind with regard to their own attachment, relative to TAU.

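### The attachment-representation outcome for hypothesis iii counts only gains of security, so it cannot register its loss or retention, and it ignores baseline AAI class

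*Protocol article*

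**What the plan says.** Hypothesis iii (Aims and hypothesis) reads: "COS intervention will improve mothers’ state of mind with regard to their own attachment, relative to TAU".

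Item d under Secondary outcomes is the analysis that addresses it. The event is defined by "those mothers with a positive shift in attachment representations [i.e., insecure (-dismissing, preoccupied, unresolved) to secure". These mothers are separated "from the mothers without such a shift or with a negative one", a negative shift being a move from secure to another class. The logistic model then has two outcome levels: "attachment representations (positive shift vs. no/negative shift) have been altered as a criterion variable". Its predictors are "treatment group (COS vs. TAU), differences of maternal psychopathology (BDI, SCL-90) as well as parenting stress (PSI) prior and after treatment as predictor variables". Baseline AAI class is not listed, and the analysis is not restricted to mothers who were insecure at baseline.

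Four other places bear on this:
- Eligibility criteria sets no AAI condition, so mothers secure at baseline can enter.
- The AAI entry under Secondary outcomes has the interview given at baseline and at follow-up.
- Randomization is stratified by infant age group only.
- Item g reuses the same coding as a predictor: "maternal attachment representations (positive shift, no/negative shift) before and after treatment, as predictor variables".

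**The concern.** A mother classified F at baseline cannot have the event. If she stays secure she is coded the same as a mother who loses security, and the same as one who was never secure. Item d can therefore detect a difference in gains but not a difference in losses or in retention. Hypothesis iii concerns the mothers' state of mind in COS relative to TAU. If COS protected security that was already present, item d would miss it. If gains in COS came with losses in COS, item d would report only the favourable half.

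Baseline class also sets the ceiling of the outcome in each arm: only the share 1 − s can contribute events. With baseline class left out of the model, a difference in s between arms passes into the comparison.

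**Working it through.** **Inputs.** From the article: the coding and predictors above, 1:1 allocation, and 36 dyads per arm (Limitations). The article gives no figure for item d, so there is none to reproduce; N = 80 belongs to the primary test and is not used here. The article does not give the share secure at baseline or the transition rates. The Background says only that such mothers are often insecure. All values of s, g and l below are assumptions. The calculations leave out the change-score covariates.

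**Formulas.** Let s = share secure at baseline, g = P(insecure to secure), l = P(secure to insecure).
- Item d event rate = (1 − s)g
- Share secure at follow-up = s(1 − l) + (1 − s)g
- Share who lose security = s·l

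The loss rate l does not appear in the first line.

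**1. Losses hidden.** s = 1/3; g = 0.40 (COS) vs 0.20 (TAU); l = 0.50 vs 0.10.
- Item d: 2/3 × 0.40 = 26.7% vs 2/3 × 0.20 = 13.3%
- Secure at follow-up: 1/3 × 0.50 + 0.267 = 43.3% vs 1/3 × 0.90 + 0.133 = 43.3%
- Losses: 1/3 × 0.50 = 16.7% vs 1/3 × 0.10 = 3.3%

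**2. Protection hidden.** s = 1/3; g = 0.25 in both arms; l = 0.05 vs 0.40.
- Item d: 16.7% in both arms
- Secure at follow-up: 1/3 × 0.95 + 0.167 = 48.3% vs 1/3 × 0.60 + 0.167 = 36.7%

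**3. Chance imbalance, identical transitions.** g = 0.30 and l = 0.10 in both arms; 6 of 36 (COS) vs 12 of 36 (TAU) secure at baseline.
- Item d: 30/36 × 0.30 = 25% vs 24/36 × 0.30 = 20%
- Secure at follow-up: 6/36 × 0.90 + 0.25 = 40% vs 12/36 × 0.90 + 0.20 = 50%
- Given this imbalance, the simulated rate of falsely favouring COS is 6.1%, against a nominal 2.5% per side.
- With s = 25%, an imbalance of 6 or more mothers in either direction occurs in about 13% of randomizations.
- Averaged over randomizations (s = 25%), the simulated error is 2.4% per side.

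**4. Dilution.** g = 0.45 vs 0.15. The item d difference is (1 − s) × 0.30: 27 points at s = 10%, 21 at 30%, 15 at 50%. Power at 36 per arm is 74%, 59% and 43%. Restricted to baseline-insecure mothers it is 76%, 65% and 50%.

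**5. What the change does to power.** Simulated trials with 36 per arm, s = 0.30, g = 0.45 vs 0.15; follow-up class is compared by a Mantel-Haenszel test stratified by baseline class.

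| Assumed effect of COS | Item d | Follow-up class, adjusted for baseline | Gains among baseline-insecure |
|---|---|---|---|
| Gains and retention (l = 0.10 vs 0.30) | 60% | 75% | 66% |
| Gains only (l = 0.20 in both) | 61% | 53% | 67% |

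In scenario 2 the adjusted analysis has about 20% power, against about 5% for item d.

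**The case against.** The hypothesis is about improvement, and moving from insecure to secure is improvement. A responder definition is a recognised choice, and the article does not call stable-secure mothers failures. That stands in part: positive shift is a sound outcome among mothers insecure at baseline. Item d, however, neither restricts to them nor adjusts for baseline class, and no companion analysis of losses is described.

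A reader might infer that any chance imbalance in baseline security turns into a false treatment effect, or that the test is anti-conservative. The documents do not support this. Randomization covers such imbalance on average, and the overall error rate is not inflated; the bias is conditional, as with any unadjusted prognostic factor. It is also usually small. At s = 0.30 the SD of the between-arm difference in baseline security is √(2 × 0.3 × 0.7/36) = 10.8 points, so with g = 0.25 a 1-SD imbalance moves the event rate by 2.7 points. An imbalance of 20% vs 40% secure is 20/10.8 = 1.85 SD, and gives 0.8 × 0.25 = 20% vs 0.6 × 0.25 = 15%. That is about 7 vs 5 mothers of 36, with p about 0.53.

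The size also depends on s, which may be low in this population. At s = 10% the SD is √(2 × 0.1 × 0.9/36) = 7.1 points and the corresponding shift is 1.8 points. Masking and dilution shrink with s as well. Finally, the trial is too small to detect much about retention under any analysis, as the 20% power in scenario 2 shows. The gain there is mainly descriptive.

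**Conclusion.** The point holds as a defect of outcome definition and model. That item d does not respond to loss or retention of security follows from its wording and needs no assumption. How much this matters rests on the share secure at baseline and on the transition rates, none of which the article gives. The scenarios show what can happen, not what is likely. Dilution is modest (59% vs 65% power at s = 30%). Imbalance is a conditional bias only.

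Item g inherits the coding, but no separate consequence has been shown there. A reader might also infer that the trial's main result is at risk. It is not, because the primary outcome is child attachment and does not use this variable. The change should be made, but the trial does not stand or fall on it.

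**What to change.** In item d, make follow-up AAI class (F vs not F) the binary outcome, compare it by arm, and include baseline AAI class (F vs not F) as a covariate. Alongside it, report by arm the gains among mothers insecure at baseline and the losses among mothers secure at baseline. The separate report is needed as well as the adjusted model: in scenario 1 follow-up security is equal in the two arms, and only the split shows that gains and losses both differ. Item g should use a coding consistent with this.

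The cost is wording in the analysis plan, since the AAI is already given at both times. The drawback is somewhat lower power if COS affects gains only (53% vs 61% in the case above). The analysis of gains among baseline-insecure mothers covers that case. Nothing here requires changing the other covariates of item d.

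### Item d, the only analysis given for secondary hypothesis iii, adjusts for post-randomisation changes in symptoms and stress, so its treatment coefficient is not the total COS-versus-TAU effect

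*Protocol article*

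**What the plan says.** Under Aims and hypothesis, the third secondary hypothesis is a between-arm claim: "COS intervention will improve mothers’ state of mind with regard to their own attachment, relative to TAU".

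The statistical section on secondary outcomes takes this up in item d. Mothers who move from an insecure or unresolved to a secure representation are separated from all others, and "a binary logistic regression will be used to compare proportions of mothers whose attachment representations (positive shift vs. no/negative shift) have been altered". The predictors are treatment group and "differences of maternal psychopathology (BDI, SCL-90) as well as parenting stress (PSI) prior and after treatment as predictor variables". No other item tests hypothesis iii; item g uses the shift as a predictor, not as an outcome. Item d mentions no unadjusted or baseline-adjusted companion analysis and does not call the model a mediation analysis.

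Two neighbouring passages bear on the point:

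- Item c states that "the differences in maternal sensitivity and mentalization will be used to predict psychopathology and maternal stress", and then adds in brackets "with treatment modality, differences in psychopathology, and differences in maternal distress as independent variables".
- Items a and b, which serve hypotheses i and ii, list "maternal psychopathology (BDI, SCL-90-R) and maternal parenting stress (PSI) as co-variables" without a time point.

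Table 1 shows BDI, SCL-90 and PSI at both baseline and follow-up.

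**The concern.** Randomisation makes the arms comparable on everything that precedes it. A pre-to-post difference contains a follow-up value, so treatment may have changed it. Holding it fixed compares COS and TAU mothers who had the same change in depression, symptoms and stress. That is a different question from whether COS improves attachment state of mind.

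Two things can go wrong:

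- Any COS benefit that works by relieving symptoms or stress is taken out of the treatment coefficient.
- If an unmeasured trait drives both symptom change and the attachment shift, mothers with equal symptom change in the two arms are no longer alike on that trait. Confounding then enters despite randomisation.

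The pathway is not remote from the authors' own thinking. The abstract names psychopathology at baseline and follow-up among the possible moderators or mediators, although there for child attachment. At stake is the conclusion on one of three named secondary hypotheses: a real COS effect could be reported as absent, or a false one suggested.

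**Working it through.** The article gives no figure for item d to reproduce. Its only design calculation concerns the primary outcome, and this point does not depend on it. It also gives neither the effect of COS on BDI, SCL-90 or PSI nor the relation of those changes to the attachment shift. Everything below except the sample size is therefore assumed and shows a range only.

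**Inputs.** N = 72, 36 per arm (Limitations). T is treatment. M is one score for symptom improvement, in SD units, standing in for the three change scores. COS shifts M by *a* SD.

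**Step 1: a continuous outcome, to show the mechanism.** With unit within-arm SDs, total effect *d* and within-arm correlation *r* between M and the outcome, the adjusted effect is *d* − *r*·*a*. For an assumed *d* = 0.6:

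- *a* = 0: 0.60 (100% kept)
- *a* = 0.5, *r* = 0.3: 0.60 − 0.15 = 0.45 (75%)
- *a* = 0.5, *r* = 0.5: 0.60 − 0.25 = 0.35 (58%)
- *a* = 0.8, *r* = 0.3: 0.60 − 0.24 = 0.36 (60%)
- *a* = 0.8, *r* = 0.5: 0.60 − 0.40 = 0.20 (33%)

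**Step 2: a logistic model like item d.** The simulated model is logit P(shift) = −0.85 + δT + βM + U, with M = *a*T + √(1 − *u*²)·e + *u*U. The term U is an unmeasured common cause, present only in the last row. Log odds ratios for COS are large-sample values (N = 20,000). Rejection rates are for the 5% test in 1,500 simulated trials of 72.

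| Scenario | Assumed inputs | Log OR without M → with M | Rejection rate at N = 72 |
|---|---|---|---|
| COS does not move M | *a* = 0, β = 0.8, δ = 1.2 | 1.06 → 1.20 | 57% → 65% |
| Partly mediated | *a* = 0.5, β = 0.8, δ = 0.8 | 1.06 → 0.81 | 58% → 33% |
| Wholly mediated, smaller shift | *a* = 0.5, β = 0.8, δ = 0 | 0.35 → −0.01 | 11% → 5% |
| Wholly mediated, larger shift | *a* = 0.8, β = 1.2, δ = 0 | 0.75 → 0.00 | 31% → 5% |
| No effect on the shift, common cause | *a* = 0.8, β = 0, δ = 0, *u* = 0.6 | about 0 → −0.41 | 5% → 10% |

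**Step 3: reading the table.** In the first row the coefficient rises because a logistic coefficient grows when a prognostic covariate is added; nothing is lost. In the mediated rows the treatment coefficient falls to the direct effect δ, which is zero when mediation is complete. In the last row, given M and T, the expected value of U is *u*(M − *a*T). This puts −0.6 × 0.8 = −0.48 on treatment before the usual logistic attenuation, consistent with the simulated −0.41. In this set-up that term is also zero when *a* = 0, so both kinds of harm need COS to move the scores.

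**The case against.** The strongest defence is that the harm is conditional. No hypothesis says that COS lowers BDI, SCL-90 or PSI. TAU is active treatment by psychiatrists and psychotherapists, and both arms may receive medication and individual psychotherapy. The arms may therefore differ little in symptom change, and then the adjustment costs nothing. This stands as a limit on size: the adjustment can remove or distort the effect, and nothing shows that it will. It does not justify the specification, because the plan cannot presume that the arms will not differ on these scores.

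It may also be said that the introductory sentence of item d implies a plain comparison of proportions, or that a separate analysis plan could supply one. But the logistic model is the only method named, and its covariates are stated, not left open.

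A reader might infer three stronger things that the article does not support:

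- **That items a and b have the same fault.** The t0–t1 notation there describes the repeated factor for sensitivity and mentalization, not the covariates. Where the authors mean change they say so, as in items c, d and e. A baseline reading is open and harmless.
- **That item c distorts a treatment effect.** It serves no stated hypothesis and is not clearly a test of treatment. Its fault is wording: psychopathology and stress appear as predicted variables and, as differences, as predictors. On another reading, changes in sensitivity and mentalization are the outcomes and the bracket lists the predictors.
- **That the COS effect will be nullified or reversed.** That takes assumptions about mediation and common causes for which the article has no figures.

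**Conclusion.** The point holds for item d. As specified, its treatment coefficient does not estimate the total effect that hypothesis iii asserts, and no other analysis of that hypothesis is given. The size is unknown. Under the assumed inputs it runs from no loss, when COS does not change the scores, to complete loss under full mediation, with a spurious negative effect possible when a common cause is present. The illustrations use one change score where item d has three.

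Item c contains a separate contradiction in wording. For items a and b no error is established; only the covariate time point needs confirming. The primary analysis is an unadjusted chi-square test and is untouched. This should be fixed, but it does not threaten the trial's main conclusion.

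**What to change.** - **Item d:** estimate the COS effect unadjusted, or adjusted only for baseline BDI, SCL-90 and PSI. Keep the change-score model, labelled as exploratory or as a mediation analysis.
- **What not to add to item d:** baseline attachment class as a covariate. A mother who is secure at baseline cannot have a positive shift, so that term would produce separation in the logistic model.
- **Item c:** name one outcome and remove that outcome, including its change score, from the predictors.
- **Items a and b:** confirm that the covariates are baseline values. The baseline outcome need not be added, since it is already the t0 level of the repeated measure.

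The cost is wording in the analysis plan. All three scales are collected at baseline (Table 1), so no new data are needed.
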